### Intervention

Participants will be randomised into one of two parallel groups: (1) an online live facilitated MBSR group or (2) a usual care control group.Participants in the online live facilitated MBSR group will participate in an 8-week intervention involving weekly 2.5-h online group sessions and one online half-day workshop. This 6-h workshop, called “The Day of Mindfulness”, will be scheduled between the sixth and seventh week, and is held in silence with only the instructor speaking. This “retreat” will provide participants with an opportunity to deepen what they learn during the weekly online sessions. Participants will be encouraged to practice mindfulness daily throughout the 8-week period. In addition, participants will receive access to a 100-page coursebook, and a mobile application called *Openground Mindfulness Training* which has pre-recorded guided meditation practices that participants can use throughout the program. Patient data and app usage data will not be sent to the mobile application developer. Participants will also receive ongoing individual support from the MBSR teacher, as necessary.

Mindfulness is defined as non-reactive awareness of the present experience, including body sensations, internal mental states, thoughts, emotions, impulses and memories [20]. Mindfulness meditation is a mind training approach that cultivates cognitive control, emotion regulation and acceptance (i.e. nonreactivity), which leads to reduced stress and increased well-being [20]. During the online MBSR program, participants will meet once a week for 2.5 h via an online platform to practice mindfulness meditation and body awareness. During this time, the participants will also interact with each other through discussions facilitated by a skilled, certified MBSR teacher. Our proposed mindfulness intervention is based on MBSR, but it has been adapted for individuals with chronic pain. This program integrates psychoeducation on the latest pain neuroscience based on the evidence-based Explain Pain program [36, 37]. Each week, the teacher presents the theoretical underpinnings of the mindfulness training and the application of self-regulatory skills and encourages dialogue and reflection on distinct topics as described in Table 1 below.

(2)Participants in the usual care control group will receive the type of care that is usually provided to individuals who are on the waitlist to attend the pain management centres at the RPAH and CRGH. This care often includes accessing brief pain education. This may be accessed through the STEPS program at the RPAH, the DIB program at the CRGH, or through My Pain Hub, a passive online evidence-based resource for musculoskeletal pain. Participants in this group will also be offered access to a passive online evidence-based educational resource for musculoskeletal pain developed by our team *My Pain Hub* (https://www.mypainhub.com). *MyPainHub* has been co-designed and developed by clinicians managing and people with musculoskeletal pain and tested in a recent RCT [38]. The patient pages contain accurate advice, information, and self-directed exercises for common musculoskeletal conditions.

**Table 1 Tab1:** Adapted from the curriculum guide for MBSR

Week	Topic	Description
1	Recognising the present moment	Safety and guidelines are established. Participants get an overview of the pain science and an introduction to mindfulness theory and practice.
2	Perception and making sense of our world	Participants begin to explore how their physical and emotional experiences can be impacted by how they perceive internal and external factors. They begin to explore how the brain creates pain as an output from danger signals.
3	Learning about pain and reactivity	Participants deepen practice and learn to approach bodily sensations with a simple appraisal of how pleasant, unpleasant or neutral they are. They learn about how pain and tissue damage are poorly related.
4	Investigating stressful experiences	Participants learn to approach difficult experiences and build emotion regulation skills through education and practice. They learn how their own meanings of safety and danger can impact their pain experience.
5	Thoughts, emotions and language	This session emphasises the capacity of participants to adapt more rapidly and effectively to everyday challenges and stressors. Participants learn how their thoughts and language can impact their pain experience. They develop more safety and confidence in relation to their inner experience.
6	Relationships and kindness	Participants actively cultivate kindness for themselves and others, enhancing resilience and connection. They learn about the complexity of the pain experience and how they can enhance their responsiveness to their own distress by allowing and letting go.
7	Values and action	Participants are asked to purposefully reflect on lifestyle choices that are adaptive and self-nourishing and those that are maladaptive and self-limiting to integrate mindfulness practice more fully and personally into their daily lives.
8	Making mindfulness a part of your life	Participants reflect on the process, celebrate their successes and grieve their disappointments. They reflect on strategies and intentions for continuing to integrate what they have learned into their lives.

### Outcome measures

#### Pilot RCT

##### Feasibility outcomes

Feasibility outcomes will include recruitment rate, retention rate, suitability of data collection methods, and identification of successful recruitment methods. Records will be kept of the number of individuals screened for eligibility, the number eligible and invited to participate, and the number that consent to participate. We will also record reasons for not entering the study and reasons for dropping out. Our pilot trial will be deemed feasible if at least 80% of the participants recruited for our pilot trial remain in the study until its completion. Our progression criteria for the trial will follow the traffic light system proposed by Avery and colleagues [39], where achieving green (go)—80% retention rate—indicates that the criteria have been met, and the trial should proceed, achieving amber (amend)—60% retention rate—indicates that some changes should be made to the larger trial and achieving red (stop)—40% retention rate—indicates that the investigators should not move forward with the larger trial. To keep a record of the issues faced during the pilot trial, we will maintain a document called ‘lessons learned’ that details the problems encountered, the attempts made to resolve them, and whether they worked or not [40].

##### Patient-reported outcome measures (PROMs)

Upon entry to the study, prior to randomisation, we will collect demographic information, including age, gender, race, ethnicity, education level, and postcode (to be used as a proxy for socioeconomic status). We will also collect information about the participant’s general health status and pain condition, including the number of years they have lived with chronic pain and their primary sources or locations of pain. Patient-reported outcome measures will be collected upon entry to the study prior to randomisation, and at the conclusion of the online MBSR program, to assess preliminary pre- to post-intervention changes. We will use the validated and widely used patient-reported outcome measures that make up the electronic Persistent Pain Outcomes Collaboration (ePPOC). The ePPOC is a resource for pain researchers and clinicians, which was established in NSW in 2013, to evaluate and assist in improving outcomes and services for people experiencing chronic pain [41]. The ePPOC measures pain and disability using the Brief Pain Inventory (BPI) [42], cognition using the Pain Self-Efficacy Questionnaire (PSEQ) [43], pain catastrophising using the Pain Catastrophising Scale (PCS) [44], mood using the Depression, Anxiety and Stress Scale (DASS-21) [45], health care utilisation and medication. These measures are recommended and used in pain management centres within Australia and New Zealand. We will also measure chronic pain acceptance using the Chronic Pain Acceptance Questionnaire (CPAQ) [46]. The CPAQ measures two aspects of chronic pain acceptance - activity engagement and pain willingness. Participants will be emailed a link to these questionnaires, which will be embedded into a web-based application (REDCap). The data collection process is illustrated in Fig. 2.

**Fig. 2 Fig2:**
[figure not shown]
Data collection flowchart

##### Adherence to the mindfulness practice

Adherence to the suggested daily mindfulness practices throughout the 8-week intervention will be measured weekly via REDCap, using an online version of the Mindfulness Adherence Questionnaire (MAQ) [47]. The MAQ is a 12-item self-reported questionnaire that captures adherence to the mindfulness practice within the past week. It was designed to assess regular and sustained practice in attentional focus and non-judgmental acceptance (i.e. quantity, quality, subtype of practice). The first two items measure the frequency and average duration (in minutes) of formal practices. The remaining 10 items measure the quality of formal practice and informal practice. Items are scored on a 7-point Likert scale ranging from 0 (never) to 6 (always), with higher total subscale scores reflecting higher practice quality.

##### Adverse events

The Meditation-Related Adverse Effects Scale - Mindfulness-Based Program version (MRAES-MBP) [48], will be used to collect data regarding adverse events. An email with a link to the MRAES-MBP embedded in REDCap will be sent to participants weekly. The MRAES-MBP scale represents the ten most common adverse events and those most highly associated with negative impacts on functioning, in the context of a mindfulness-based program, specifically: signs of hyperarousal (anxiety, perceptual hypersensitivity, traumatic re-experiencing, emotional lability, insomnia), hypo-arousal/blunting (anhedonia, depersonalisation), executive dysfunction and social disengagement [48]. If a participant reports experiencing distress that is impairing their ability to function, they will receive a phone call from our MBSR program teacher, who is an experienced Medical Doctor with extended skills in psychological medicine and a special interest in mindfulness-based interventions, complex trauma and the psychological aspects of chronic pain. Depending on the severity of the distress and the level of impact on functioning, the meditation practices may need to be adjusted or discontinued, or the participant may be advised to discontinue the intervention altogether. Where appropriate, the participant will be referred to the psychologist at the RPAH or CRGH pain management centres.

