Mindfulness-based stress reduction (MBSR) is a mind-body training program developed specifically to address the distress associated with long-term conditions, such as chronic pain [19]. The MBSR program combines mindfulness meditation, body awareness, yoga, and exploration of patterns of behaviour, thinking, feeling and action [20]. By engaging participants holistically on multiple levels (i.e. physiological and emotional regulation, cognitive reappraisal, behavioural change, engagement with values, and social connection), MBSR has been shown to significantly reduce pain [21, 22], improve symptoms of anxiety, and depression and improve quality of life, in people with various chronic conditions [23], including chronic musculoskeletal pain [22–24]. MBSR is typically delivered as a face-to-face, 8-week program, with weekly 2.5-h group sessions, and an expectation of daily practice by participants [20]. However, recent evidence has shown that online delivery of MBSR is comparably effective to in-person delivery [25]. An online delivery mode allows participants to complete the program without the need to travel to a single location, which can pose logistical and financial challenges [26].

Despite evidence supporting the efficacy of MBSR in improving patient-reported outcomes for chronic pain [21], availability to patients in Australia remains limited. MBSR programs are primarily offered as privately funded courses, which are costly thereby excluding a large proportion of patients with chronic musculoskeletal who cannot afford it [27]. Addressing this barrier to access calls for the incorporation of MBSR programs into the public health system [28]. This shift could improve access to a mind-body approach that can improve the well-being of patients with chronic musculoskeletal pain, thereby mitigating health inequities. However, implementing a novel intervention in health services requires significant and planned changes, and the first step is to test its practicality [29]. In this context, pilot studies play a crucial role in testing and refining the research methods and procedures prior to a fully powered clinical trial. Pilot trials further assist in identifying potential barriers and facilitators related to the intervention, enable assessment of the feasibility of data collection and analysis, and by uncovering any issues early on, guide necessary adjustments that improve the quality and efficiency of fully powered clinical trials [30].

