Our study, therefore, aims to (1) evaluate the feasibility of an online MBSR program for managing chronic musculoskeletal pain within the public health care system in Australia; (2) identify barriers and facilitators related to the online MBSR program for people with chronic musculoskeletal pain; and (3) determine the preliminary efficacy and safety of the online MBSR program compared to usual care on patient-reported outcomes.

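### Safety is to be compared with usual care, but the only adverse-event tool named is a meditation-specific scale, and its use in the control arm is not stated

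*Protocol article*

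**What the plan says.** The Background ends with three aims. The third is to "determine the preliminary efficacy and safety of the online MBSR program compared to usual care on patient-reported outcomes". Safety is therefore framed as a comparison between arms, although a preliminary one.

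The Adverse events section names one instrument: "The Meditation-Related Adverse Effects Scale - Mindfulness-Based Program version (MRAES-MBP) [48], will be used to collect data regarding adverse events". On delivery it says: "An email with a link to the MRAES-MBP embedded in REDCap will be sent to participants weekly". It describes the events covered as those seen "in the context of a mindfulness-based program", and lists them as "signs of hyperarousal (anxiety, perceptual hypersensitivity, traumatic re-experiencing, emotional lability, insomnia), hypo-arousal/blunting (anhedonia, depersonalisation), executive dysfunction and social disengagement". Distress that impairs function leads to a phone call from the MBSR teacher, after which "the meditation practices may need to be adjusted or discontinued, or the participant may be advised to discontinue the intervention altogether".

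The comparator is described in the Intervention section: "Participants in the usual care control group will receive the type of care that is usually provided to individuals who are on the waitlist". No meditation is described for that arm.

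Two related measures appear under Patient-reported outcome measures. The Brief Pain Inventory (BPI) and the DASS-21 are collected before randomisation and again when the programme ends. The Data analysis section plans intention-to-treat comparisons between groups for patient-reported outcomes.

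**The concern.** A comparison of harms between arms needs the same questions, put in the same way and equally often, to both arms. Otherwise a difference in counts may reflect how events were sought rather than what happened.

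This matters more than usual here. The Background says that people with chronic musculoskeletal pain often carry high emotional distress and that long waits can make it worse. Several symptoms on the scale, such as anxiety, insomnia and anhedonia, are the kind such patients may report without any meditation. Without parallel, neutrally asked control data, it is hard to judge how far weekly reports in the MBSR arm reflect the programme and how far they reflect the condition and the wait.

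**Working it through.** **1. Aim against instrument.** The aim names usual care as the comparator for safety. The one event instrument is defined by its setting in mindfulness programmes. The described response to a report (changing the meditation practices, or advising the person to stop the intervention) can apply only to someone receiving MBSR.

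**2. Who completes the scale.** The text says *participants*, and the article uses that word in both senses. The Intervention section uses it for the MBSR arm alone when it encourages daily practice, and the same section also applies it to controls. The Data analysis section lists mindfulness adherence among the outcomes for between-group comparison, although no mindfulness practice is described for usual care. The article's wording therefore does not settle arm coverage.

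**3. The two readings.**
- MBSR arm only: no event-level data exist for usual care, and the comparison in the aim cannot be made from this tool.
- Both arms: control data exist, but from a scale built and titled for meditation effects. Controls may answer it differently from people who are meditating, so the comparison is open to ascertainment bias.

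**4. What the other measures add.** The BPI and DASS-21 are measured in both arms at two time points. They can show worsening of pain or mood by arm. They do not record events arising and resolving between those points, or events of other kinds.

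**5. Precision if both arms are asked the same questions.** The plan gives no adverse-event rate, margin or precision, so there is no stated figure to reproduce. From the Sample size section, n = 16 per arm. The true proportion p with at least one event is assumed equal in both arms. The Wald 95% half-width for the difference is 1.96 × √(2p(1 − p)/16).

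| Assumed p | Calculation | Half-width |
|---|---|---|
| 10% | 1.96 × √(0.18/16) | ±20.8 points |
| 20% | 1.96 × √(0.32/16) | ±27.7 points |
| 30% | 1.96 × √(0.42/16) | ±31.8 points |
| 50% | 1.96 × √(0.50/16) | ±34.6 points |

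These figures assume that all 32 contribute data; losses would widen them. The Wald formula is rough at such small counts but gives the scale.

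**6. Precision if safety is described in the MBSR arm alone.** With zero events in 16, the exact two-sided 95% upper limit is 1 − 0.025^(1/16) = 20.6%.

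**7. Illustration of background reporting.** Assume a 5% to 10% weekly chance of a symptom unrelated to MBSR, and independent weeks. Over 8 weekly forms, 1 − 0.95⁸ = 34% to 1 − 0.90⁸ = 57% would report it at least once, or 5 to 9 of 16. Neither rate comes from the documents. Persistent symptoms make independence doubtful, and positive correlation between weeks would lower these figures. They show only why a control rate is useful.

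**The case against.** A reader might infer that the trial will have no comparator rate at all. The documents do not support that. The scale goes to participants without restriction to one arm, and the data collection flowchart (Fig. 2), which could not be seen here, may show which arm gets which form. Several listed symptoms can be reported by someone who does not meditate. The item wording is not given, so whether items ask for attribution to meditation cannot be checked.

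A reader might also infer that the scale misses injuries from yoga in this trial. The Background does say: "The MBSR program combines mindfulness meditation, body awareness, yoga, and exploration of patterns of behaviour, thinking, feeling and action". That describes MBSR in general. The trial's programme is an adapted version, and neither its description under Intervention nor Table 1 mentions yoga.

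Further points on the other side are fair:
- The article condenses a full protocol, which may contain general adverse-event procedures. Their absence from the article is weak evidence.
- A data safety monitoring board (DSMB) will discuss the format and content of its reports. Reasons for dropping out are recorded, and MBSR participants are interviewed.
- The aim is preliminary, and the progression criteria rest on retention, so no stated decision turns on an adverse-event difference.
- At 16 per arm a comparison is weak whatever form is used: power is about 23% for assumed rates of 20% against 40%, and 29% for 10% against 30%.

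These points limit the strength of the claim. They do not remove the mismatch between a comparative aim and a tool designed for one arm's treatment. Low precision is a reason to describe the comparison cautiously, not to ask the arms different questions.

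**Conclusion.** The point holds in a limited form. The article sets a comparative safety aim, names only a meditation-specific scale for events, leaves its use in the control arm unstated, and describes a response that presumes MBSR exposure. Depending on the intended coverage, the event-level comparison is either unavailable or weakly founded.

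The gain from correcting this is a like-for-like comparison, not a precise one: about ±21 points at an assumed 10% per arm and ±32 points at an assumed 30%. The conclusion rests on the article alone; the full protocol or Fig. 2 could settle arm coverage. It is a cheap improvement worth making and does not threaten the feasibility objective.

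**What to change.** State which arms complete the scale. Then do one of the following.

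**Preferred.** Send both arms the same weekly REDCap form.
- Ask about the listed symptoms over the past week without attributing them to meditation. The section announces ten events but names nine, so take the list from the scale itself.
- Add increased pain and one open item for any other event.
- Keep any meditation-attribution questions as an add-on for the MBSR arm.
- Report by arm the number with at least one event, and the difference with a 95% confidence interval, described as imprecise. A score-based interval suits these counts better than the Wald formula.

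**Alternative.** Remove the comparison with usual care from the safety aim and describe safety within the MBSR arm only.

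The preferred route uses the weekly delivery already in place. It costs a short weekly form for about 16 controls and a minor amendment. The alternative costs only a change of wording.

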### Qualitative study

#### Acceptability, and barriers and facilitators of engagement

Qualitative data, collected through in-depth interviews, will explore participants’ experiences with the MBSR program, focusing on barriers and facilitators to engagement and the acceptability of the intervention. Qualitative research is essential for capturing the lived experiences of participants, offering insights that quantitative measures alone cannot provide. By examining participants’ perspectives, we can identify key factors influencing participation, refine the intervention to enhance accessibility and adherence, and inform future implementation strategies [34]. The investigators conducting these in-depth interviews will be independent from the MBSR program. Additionally, the interviewees will not know the investigators conducting these in-depth interviews. All interviews will be audio-recorded and transcribed verbatim.

### Sample size

#### Pilot RCT

Decisions about sample size in pilot studies can be challenging as a variety of approaches exist [49–52]. Some researchers suggest that pilot studies should include at least 30 participants to provide a reliable estimate of the standard deviation, which is essential for calculating the sample size of a future full-scale trial [51]. Based on these guidelines, we plan to recruit 32 participants (approximately 16 per group) for this pilot study. This represents 9% of the estimated sample size for the full trial, which is the minimum threshold recommended by Cocks and Torgerson (2013) [50]. This sample size provides >80% confidence in determining whether to proceed with a full trial, aligning with feasibility objectives. The calculation is based on an estimated effect size difference for the full trial, using a confidence interval approach [50]. A key feasibility outcome is the retention rate, which we anticipate to be 80%. Given our sample size (*N*= 32), this can be estimated to be within approximately ±15% with 95% confidence, meaning that around 26 participants are expected to complete the study [39]. However, we acknowledge that this estimate is provisional and will be refined based on feasibility data collected from the pilot study, including actual retention rates, standard deviation estimates, and adherence metrics.

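### The stated >80% confidence in the decision to proceed comes from an effect-size interval that no progression rule uses; the retention rule that does decide turns green about 54% of the time at the anticipated retention, and the 30-participant minimum for the SD is met only before dropout

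*Protocol article*

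**What the plan says.** The Sample size section (Pilot RCT) of the protocol article gives three reasons for its number, "we plan to recruit 32 participants (approximately 16 per group) for this pilot study".

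- A rule of thumb on the standard deviation: "pilot studies should include at least 30 participants to provide a reliable estimate of the standard deviation".
- A share of the later trial: "This represents 9% of the estimated sample size for the full trial, which is the minimum threshold" in the cited guidance.
- A decision property: "This sample size provides >80% confidence in determining whether to proceed with a full trial, aligning with feasibility objectives". The next sentence gives its basis: "The calculation is based on an estimated effect size difference for the full trial, using a confidence interval approach".

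The same paragraph anticipates 80% retention, estimated to within about 15 percentage points, so that "around 26 participants are expected to complete the study".

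The progression criteria are under Feasibility outcomes. They use retention alone: "achieving green (go)—80% retention rate—indicates that the criteria have been met", with amber at 60% and red at 40%. That section also calls the pilot feasible if at least 80% of those recruited stay to the end. The Data analysis section reports patient-reported outcomes as mean differences with 95% intervals. It uses effect sizes and variability to plan the full trial and attaches no go/stop rule to them.

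**The concern.** There are two problems.

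First, a confidence level is stated for the decision whether to proceed, but it is calculated for a quantity that does not enter that decision. A funder or ethics committee could take the go decision to be more than 80% reliable, although the rule that will be applied has quite different properties.

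Second, the minimum for the SD is compared with the number recruited. Patient-reported outcomes are collected only at baseline and at the end of the program. The follow-up SDs and between-group differences that feed the next sample-size calculation therefore come from those who supply follow-up data, about 26 by the article's own expectation.

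**Working it through.** **Inputs.** From the Sample size section: N = 32, 16 per arm; 9% of the full trial; anticipated retention 80%; SD minimum 30. From Feasibility outcomes: green at 80% retention or more. The article does not give the full-trial N, effect size, alpha or power. I assume two-sided 5% and show 80% and 90% power.

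**1. The article's own figures.**
- Completers: 0.80 × 32 = 25.6, about 26. This agrees.
- Half-width for retention: 1.96 × √(0.8 × 0.2/32) = 0.139, consistent with about ±15 points.
- Implied full trial: 32/0.09 = 355.6, about 356.
- Detectable standardised effect: d = (1.960 + z_power) × √(4/355.6), which is 0.297 at 80% power (z = 0.842) and 0.344 at 90% power (z = 1.282).
- One-sided confidence with n analysed in the pilot: Φ(d/√(4/n)). For n = 32, √(4/32) = 0.354, giving Φ(0.841) = 80.0% or Φ(0.972) = 83.5%.

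So the >80% can be reproduced, to rounding at 80% power, as a statement about an effect-size interval with all 32 analysed.

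**2. The rule that decides progression.** 25/32 = 78.1% and 26/32 = 81.3%, so green needs at least 26. With X ~ Binomial(32, p):

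| True retention p | P(X ≥ 26) |
|---|---|
| 70% | 11.3% |
| 75% | 27.8% |
| 80% (anticipated) | 53.5% |
| 85% | 80.5% |
| 90% | 96.4% |

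The value near one half at 80% arises because the threshold equals the anticipated rate. Of these values, only 85% and 90% give a probability of green above 80%.

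**3. The SD minimum.** With X ~ Binomial(32, 0.80), P(X ≥ 30) = 3.2%. The 95% limits for a pooled SD, as multiples of the estimate, are √(df/χ²) at the 97.5% and 2.5% points, with df = n − 2:
- n = 32: 0.80 to 1.34
- n = 26: 0.78 to 1.39

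Baseline SDs can use all 32.

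**4. The 9% and the >80% after dropout.** The result depends on what the 356 counts.

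| Meaning of 356 | Pilot share | Confidence, 80% power | Confidence, 90% power |
|---|---|---|---|
| Analysed | 26/355.6 = 7.3% | Φ(0.297/0.392) = 77.6% | Φ(0.344/0.392) = 81.0% |
| Recruited, same 20% loss (284.4 analysed) | 26/284.4 = 9.1% | Φ(0.332/0.392) = 80.2% | Φ(0.384/0.392) = 83.6% |

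Here √(4/26) = 0.392. In the second row, d is recomputed from 284.4. Confidences were computed from unrounded values.

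**The case against.** The strongest reply is that the article never claims 80% confidence for the retention rule, since it names the effect-size basis in the very next sentence. That is right. A reader might infer that the article miscalculated the reliability of its retention rule; it did not, and the 54% contradicts no stated figure. What stands is narrower: the sentence describes the decision to proceed, and the only rule shown for that decision is retention.

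A reader might also infer that dropout breaks the 9% and the >80%. The document does not support that. If the implied full-trial size is a recruited number with the same loss, both survive; even if it is an analysed number, 90% power leaves 81.0%.

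Nor is it fair to say that attrition is ignored. The 26 completers are stated, the retention precision correctly uses all 32, and the estimate is called provisional. The cited minimum of 30 may also have been meant for recruits, which cannot be checked here. But its stated purpose is a reliable SD for planning, and a follow-up SD can come only from people with follow-up data. The loss of precision is small, and that limits the weight of this part.

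Finally, an article condenses the full protocol, which could hold an effect-size criterion or the missing assumptions. Their absence is therefore not the point. The point is that the article's text puts a confidence level on a decision that its own criteria make by other means.

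**Conclusion.** The sentence is wrong as written. The >80% belongs to an effect-size interval, whereas the stated progression rule has a 54% chance of green at the anticipated retention, and between 11% and 81% for true retention from 70% to 85%. These probabilities assume independent dropout with a common rate and green read as at least 26 of 32.

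The SD minimum is met by recruits only. Among expected completers it is missed (26 against 30, with about a 3% chance of reaching 30), at a modest cost in precision and none for baseline SDs. Whether the 9% and the >80% hold after dropout is undetermined on the document's figures.

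Severity is minor to moderate. The sample size itself need not change.

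**What to change.** Keep N = 32 and amend the Sample size text:

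1. Delete the sentence on confidence in determining whether to proceed, or limit it to the effect-size interval and state the assumed effect, the full-trial power and the number analysed.
2. Restate the SD justification on about 26 completers, with limits of about 0.78 to 1.39 times the estimate, noting that baseline SDs use all 32.
3. Say whether the 9% refers to recruited or analysed participants, in the pilot and in the full trial.
4. Give the probability of green over a range of true retention, as in the table above, as the stated reliability of the progression decision.

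The cost is wording and slightly less favourable stated figures, with no extra patients. If the sponsor would rather meet the minimum of 30 among completers, 20% loss implies recruiting 30/0.8 = 37.5, so 38; that is an option and not needed for this correction.
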